### Outcome Measures

#### Primary Outcomes

The primary outcome is the change in participants’ KAP toward antibiotics use and AMR 6-10 weeks post intervention from the baseline, measured by the KAP survey. We developed the KAP survey by assessing the literature [9,21,25] and adapting questions from the World Health Organization’s multicountry public awareness survey on antibiotic resistance [12]. Our KAP survey comprises 11 knowledge items with binary responses and 14 three-point Likert-scale items assessing participants’ attitudes and perceptions on antibiotics use and AMR (Table 1). We reverse-scored a few knowledge items in the postgame and postintervention surveys to reduce memory effects on knowledge gains.

**Table 1 table1:** Knowledge, attitudes, and perception survey items.

Item number			Items		Response options
**Knowledge items**					True and false
	1	If bacteria are resistant to antibiotics, it can be very difficult or impossible to treat the infections they cause.			
	2	It is okay to buy the same antibiotics or request for them from a doctor, if they had helped you get better previously when you had the same symptoms.			
	3	It is okay to use antibiotics that were given to a friend or family member, as long as they were used to treat the same illness.			
	4	I can stop my antibiotics course when I start feeling better.			
	5	Antibiotic resistance is an issue that could affect me or my family.			
	6	Antibiotic resistance is only a problem for people who take antibiotics regularly.			
	7	Many infections are becoming increasingly resistant to antibiotics treatment.			
	8	Antibiotic resistance is an issue in other countries and in Singapore.			
	9	Antibiotic resistance occurs when your body becomes resistant to antibiotics and antibiotics no longer work as well.			
	10	Bacteria which are resistant to antibiotics can spread from person to person.			
	11	Antibiotic-resistant infections could make medical procedures like surgery, organ transplant, and cancer treatment much more dangerous.			
**Statements on attitudes and perceptions**					Agree, disagree, and unsure
	12	I feel that there is no harm in taking antibiotics.			
	13	I need antibiotics to help me to recover faster from the common cold and flu.			
	14	I need antibiotics to help me to recover from serious symptoms of the common cold and flu.			
	15	I need antibiotics if I continue to have flu symptoms after 2 weeks.			
	16	I will keep leftover antibiotics for future use if I have similar symptoms.			
	17	I would stop my course of antibiotics if I am concurrently using alternative remedy (eg, Traditional Chinese Medicine, Ayurveda medicine, Jamu).			
	18	I am scared of getting antibiotic resistance infections.			
	19	I will see another doctor if my doctor does not give me antibiotics.			
	20	How I use antibiotics does not affect my chances of getting antibiotic resistance infections.			
	21	How I use antibiotics does not affect other people’s chance of getting antibiotic resistance infections.			
	22	I normally keep antibiotic stocks at home in case of emergency.			
	23	If my family member is sick, I will usually give my antibiotics to them.			
	24	I normally stop taking antibiotics when I start feeling better.			
	25	I will take leftover antibiotics when I think I need them.			

#### Secondary Outcomes

The secondary outcomes are the assessment of the user engagement level (tracked by time spent on the app) and satisfaction level of playing the game (via the immediate postintervention survey). The satisfaction survey will also collect participants’ feedback on the game app.

### Sample Size

Based on 2 meta-analyses, the effect size of serious games on improving the knowledge of chronic disease management among young people is 0.361 (95% CI 0.098-0.624) [26] and healthy lifestyle promotion in general is 0.334 (95% CI 0.260-0.407) [27]. Using the smaller 2-tailed effect size of 0.334 with a 1:1 allocation ratio, a minimum sample size of 142 per group is required to detect significant changes in knowledge at a power of 80% and an α level of .05. Assuming an attrition rate of 30%, we will require a sample size of 200 participants per group for the study.

### Statistical Analysis

We will analyze the changes in the KAP scores with multivariable linear regression models and app satisfaction levels among intervention group participants with descriptive analyses. We will also conduct a post hoc power analysis to ensure that the sample size used in our study is adequately powered to detect a significant change.

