### Potential Limitations

Health promotion efforts to improve the public’s knowledge of antibiotics use are ongoing in Singapore via traditional mass media such as posters, advertisements, and billboards. These advertisements may contaminate and dilute the effects of our intervention but should not have a measurable impact on our study as the study period falls outside the national “antibiotic awareness week” campaign. Participants with good baseline knowledge may not see knowledge improvement due to the ceiling effect. We anticipate this problem to be minor, as a recent national study found that knowledge of good antibiotic use and AMR is poor among the population.

We will also ensure that only 1 adult from each household can participate in the study to minimize the possibility of contamination due to randomization (ie, 1 member is randomized into the control group and another into the intervention group). However, we would not be able to ensure that the recruited participant is the person completing the quest in the app, as family members (ie, children) may help to complete the game quest.

Older adults who are not technologically astute may also be excluded from our study or face difficulty in completing the game quest even if they meet the inclusion criteria. We will report problems with recruitment and follow-up and conduct subgroup analyses to assess outcomes between older and younger participants.

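### The change-score regression does not commit to adjusting for baseline score; without that adjustment the arm comparison is less precise than data already collected allow

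*Protocol article*

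**What the plan says.** The outcome is defined as a change. Under Primary Outcomes: "The primary outcome is the change in participants’ KAP toward antibiotics use and AMR 6-10 weeks post intervention from the baseline". The Statistical Analysis section gives the model in one clause: "We will analyze the changes in the KAP scores with multivariable linear regression models". No covariates are listed, so the baseline score is neither included nor excluded. Under Study Procedures, both arms complete the baseline KAP survey.

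Three other statements bear on the choice:

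- **Sample Size.** The target is framed on knowledge: "a minimum sample size of 142 per group is required to detect significant changes in knowledge". The standardised effect is 0.334. The article does not say whether that is in units of the score's SD or of the SD of change, and it gives no baseline to follow-up correlation.
- **Potential Limitations.** The authors foresee that change will depend on the starting level: "Participants with good baseline knowledge may not see knowledge improvement due to the ceiling effect". They expect this to be minor. The response stated there is a subgroup comparison of older and younger participants, and the abstract's conclusions likewise rely on subgroup analyses to deal with confounding.
- **Primary Outcomes.** The knowledge items are not identical at the two surveys: "We reverse-scored a few knowledge items in the postgame and postintervention surveys to reduce memory effects on knowledge gains". No such alteration is stated for the 14 attitude and perception items.

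**The concern.** A raw change score carries the measurement noise of both surveys. It is also usually negatively related to the starting value: people who score high at baseline have little room to rise, and people who score low by chance tend to drift up. Conditioning on the baseline score removes that dependence. A subgroup analysis by age does not, because age is not the baseline score.

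Two things are at stake if the clause is followed literally with baseline left out. The first is precision: the confidence interval for the arm difference is wider than it need be. The second is chance imbalance. If the arms happen to start apart by D, the unadjusted change estimate moves by about −(1−rho)·D, whereas the adjusted estimate does not. Randomisation makes D zero on average but not in the one trial that is run.

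The planned numbers leave little reserve. The evaluable number after the assumed attrition sits just under the article's own minimum.

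**Working it through.** **Inputs from the Sample Size section.** Standardised effect 0.334; two-sided, 1:1; 80% power and alpha .05; minimum 142 per group; 30% attrition; 200 enrolled per group. **Assumed, because the article does not give it:** rho, shown from 0.3 to 0.7, and equal SDs at the two surveys.

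**1. Reproduce the plan's figure.** n per group = 2(1.960 + 0.842)² / 0.334² = 140.7, so 141 by the normal approximation. The two-sample t-test gives 141.68, so 142, as stated. Inflating, 142/0.70 = 203 against the stated 200, a small difference. Evaluable per arm = 200 × 0.70 = 140, which gives 79.8% power.

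**2. Residual variance under the two analyses** (score SD = 1):

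- unadjusted change: 2(1−rho)
- adjusted for baseline: 1−rho²
- ratio: 2(1−rho)/(1−rho²) = 2/(1+rho)

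This is 1.54 at rho 0.3, 1.33 at 0.5 and 1.18 at 0.7. The difference between the two variances is (1−rho)², which is positive for any rho below 1.

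**3. Power at 140 per arm, 0.334 on the score SD.** Power = Φ(0.334·√(140/2)/s − 1.960), with s the residual SD. The unscaled term is 0.334 × 8.367 = 2.794.

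| rho | s, change | power, change | s, adjusted | power, adjusted | n per arm for 80%: change / adjusted |
|---|---|---|---|---|---|
| 0.3 | 1.183 | 65.6% | 0.954 | 83.4% | 198 / 129 |
| 0.4 | 1.095 | 72.3% | 0.917 | 86.2% | 169 / 119 |
| 0.5 | 1.000 | 79.8% | 0.866 | 89.7% | 141 / 106 |
| 0.6 | 0.894 | 87.8% | 0.800 | 93.7% | 113 / 91 |
| 0.7 | 0.775 | 95.0% | 0.714 | 97.5% | 85 / 72 |

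Comparing follow-up scores alone, ignoring baseline, gives 79.8% throughout. Below rho 0.5, unadjusted change does worse than that.

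**4. Power at 140 per arm, 0.334 on the change SD.** Unadjusted change has s = 1 and power 79.8% whatever rho is. Adjusted analysis has s = √((1+rho)/2), giving 93.4% at rho 0.3, 89.7% at 0.5 and 85.8% at 0.7.

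**5. Does it matter which outcome is put on the left-hand side?** Not if baseline is in the model. Subtracting baseline from the outcome lowers the baseline coefficient by exactly 1 and leaves the arm coefficient alone. In one simulated data set of 280 participants (rho 0.5), follow-up regressed on arm and baseline, and change regressed on arm and baseline, both gave 0.4725 with SE 0.0957. Change on arm alone gave 0.4982 with SE 0.1080. The gap of 0.0257 is that sample's chance baseline imbalance coming through.

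**6. Do the altered items shift the comparison?** Adding a constant form effect to both arms at follow-up left the unadjusted change estimate at 0.4982, SE 0.1080: no effect on the arm difference.

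**The case against.** The strongest reply is that the article does not commit to an unadjusted analysis. It says multivariable, so covariates are intended, and step 5 shows that a change model containing baseline is the same analysis as a baseline-adjusted follow-up model. A covariate list is something a condensed article may leave to a fuller plan. This stands to the extent that a reader might infer that the authors chose change in place of baseline adjustment, and the text does not support that. What remains is that the article fixes change as the outcome, foresees that change depends on baseline, and offers only subgroup analyses in response. Two analysts could both follow the clause and report estimates of materially different precision.

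A second reply is that a power shortfall needs several undocumented conditions at once: baseline omitted, rho below about 0.5, and 0.334 expressed on the score SD. This also stands. On the change-SD reading the planned power is met without adjustment, and at rho 0.6 or 0.7 unadjusted change exceeds 80% on either reading except the change-SD one, where it stays at the planned 79.8%. So the trial cannot be called underpowered on this ground. Adjustment nevertheless gains under both readings at every rho shown.

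A third concerns the altered knowledge items. A reader might infer that subtracting a different baseline form biases the result. If both arms receive the same follow-up form, and nothing in Study Procedures or Primary Outcomes suggests otherwise, a common shift cancels (step 6). The text also speaks of reverse-scoring; that the items were reworded is an inference. What is left is narrower: altered items may lower rho for the knowledge score, and they make within-arm change harder to read.

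**Conclusion.** The point holds as an improvement to the stated method. The analysis clause does not secure baseline adjustment, and without it the arm comparison has 2/(1+rho) times the adjusted variance and is exposed to chance baseline imbalance.

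The size depends on a correlation the article does not give. Over rho 0.3 to 0.7, the power gained by adjusting at 140 per arm runs from about 18 points (65.6% to 83.4%) down to 2.5 points (95.0% to 97.5%) if 0.334 is on the score SD. If it is on the change SD, the gain runs from about 14 points (79.8% to 93.4%) down to 6 (79.8% to 85.8%). These figures assume equal SDs at the two surveys, a linear relation between them and a large-sample approximation. A marked ceiling would strain the first two assumptions.

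The check reproduces the sample size of 142 per group and does not show it to be wrong. It shows no bias between arms from the altered items, and it does not show that baseline has been excluded from the model.

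**What to change.** State in the Statistical Analysis section that the primary model is a linear regression of the 6-10 week score on randomised arm, with the same participant's baseline score as a pre-specified covariate. The adjusted arm difference should be reported with its 95% CI. If the authors prefer to keep change as the outcome, they can: with baseline in the model the arm effect and its standard error are identical. Within-arm change in knowledge should be reported descriptively, with a note that some items were altered after baseline.

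The cost is one sentence, settled before outcome data are examined. No new data are needed and the sample size need not change. If a fuller plan already names baseline as a covariate, the sentence simply makes that explicit.

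### The planned post hoc power analysis cannot ensure adequate power and, if run at the observed effect, would add nothing to the p-value

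*Protocol article*

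**What the plan says.** The Sample Size section of the protocol article fixes the size of the trial before any data are seen. It takes the lower of two meta-analytic effects, "Using the smaller 2-tailed effect size of 0.334 with a 1:1 allocation ratio", and concludes that "a minimum sample size of 142 per group is required to detect significant changes in knowledge". The target power is 80% and the significance level 5%. It then allows for losses: "Assuming an attrition rate of 30%, we will require a sample size of 200 participants per group for the study".

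The Statistical Analysis section names the analysis of the main outcome: "We will analyze the changes in the KAP scores with multivariable linear regression models". It goes on: "We will also conduct a post hoc power analysis to ensure that the sample size used in our study is adequately powered", the target being detection of a significant change.

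The article does not say whether the post hoc calculation will use the observed effect or the planned 0.334. It describes no interim look or sample-size re-estimation that could act on the answer, and no other section qualifies the sentence.

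**The concern.** The sentence gives the calculation a purpose that it cannot serve. Once follow-up has ended the number of participants is fixed, so nothing computed from the data can make the sample adequate.

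In its usual form, power evaluated at the effect that was observed, the calculation does not check adequacy either, because it is a transformation of the p-value. A small observed effect gives a low figure by construction.

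What is at stake is how a null or small result is read. The article raises possible ceiling effects (though it expects them to be minor) and plans for 30% attrition, so such a result is plausible. A low post hoc figure would suggest that the trial was too small, when the useful question is whether the data rule out the effect it was designed to find.

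**Working it through.** **Inputs** (Sample Size section): standardised effect d = 0.334, two-sided α = 0.05, power 80%, 1:1 allocation, 142 per group, 30% attrition, 200 per group recruited.

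**1. The plan's own figure.**
- Normal approximation: n = 2(1.960 + 0.842)²/0.334² = 140.7, so 141 per group.
- Two-sample t-test: 141.7, so 142 per group, as stated (power 80.1%).
- Attrition: 142/0.70 = 202.9, so 203 against the stated 200. From 200, a 30% loss leaves 140.
- Power at 140 per group: Φ(0.334 × √(140/2) − 1.960) = Φ(2.794 − 1.960) = 79.8%. The shortfall from 203 is immaterial.

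The a priori calculation is sound.

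**2. Post hoc power at the observed effect.** Let z_p be the normal deviate for a two-sided p-value. Then

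observed power = Φ(z_p − 1.960) + Φ(−z_p − 1.960).

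Neither the sample size nor the planned effect enters except through p.

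| p | z_p | observed power |
|---|---|---|
| 0.001 | 3.291 | 91% |
| 0.01 | 2.576 | 73% |
| 0.05 | 1.960 | 50% |
| 0.10 | 1.645 | 38% |
| 0.20 | 1.282 | 25% |
| 0.50 | 0.674 | 10% |

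To reach 80%, z_p must be about 1.960 + 0.842 = 2.802, which is p of about 0.005. Significant results with p between about 0.005 and 0.05 therefore fall between 50% and 80%.

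**3. Conflict with the design.** Take 140 per group and an observed d of 0.20. Then z = 0.20 × √70 = 1.673, p = 0.094 and observed power is 38.7%. Power at the planned effect, with the same participants, is 79.8%.

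**4. What the confidence interval would show.** With 140 per group the 95% half-width is 1.96 × √(2/140) = 0.234 SD. The interval excludes 0.334 when the observed d is below 0.334 − 0.234 = 0.100. For an observed d of 0.05:
- The interval is −0.184 to 0.284, so the planned effect is excluded.
- z = 0.05 × √70 = 0.418 and p = 0.68.
- Observed power is Φ(−1.542) + Φ(−2.378) = 0.062 + 0.009, about 7%.

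The interval says that the planned effect is unlikely. The power figure would suggest that the trial was too small to tell.

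**5. Power at the planned effect and the achieved number.** At d = 0.334 the normal approximation gives 65.6% with 100 per group, 73.5% with 120, 79.8% with 140 and 91.6% with 200. This version reflects actual attrition and does not depend on the observed result.

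**The case against.** The strongest reply is that the sentence may not mean power at the observed effect. It refers to the sample size used in the study, and with 30% attrition expected the authors may intend to recompute power at 0.334 with the number who complete. That would not restate the p-value, and the article does not rule it out. This stands, so the equivalence with the p-value is conditional. The objection to the stated purpose is not: that version could describe the power achieved, but it could not ensure it.

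Two stronger readings should be resisted.
- A reader might infer that any significant result would automatically appear adequately powered. It would not. At p = 0.01 the observed power is 73%, below the article's own 80% standard.
- A reader might infer that the authors will qualify their conclusions by the power figure. The article ties it to no interpretation or decision rule, so misreading is a risk and not a stated plan.

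It is also fair to say that a condensed article may leave the reporting of confidence intervals to a fuller document. Their absence is not the fault here. The fault is an analysis that is stated and cannot do what is claimed for it.

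Finally, 0.334 was planned for knowledge only, while the regression covers all the KAP scores. Comparing an interval with 0.334 has no planned basis for attitudes and perceptions. That is correct and limits the remedy.

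**Conclusion.** The point holds in conditional form. Whichever effect is used, a calculation after data collection cannot ensure adequate power. If the observed effect is used, the result is fixed by the p-value, and a non-significant trial must show about 50% or less even though design power with 140 per group is 79.8%.

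The figures assume a two-sided 5% test with an approximately normal statistic. The confidence-interval examples also assume an unadjusted comparison of two equal groups of 140, with the effect in SD units. Covariate adjustment would change the interval width, but not the link between observed power and the p-value beyond small-sample detail.

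Severity is modest. The sample size, the regression model, the primary estimate and its test are all untouched. What could suffer is the reading of a null or borderline result.

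**What to change.** Delete the post hoc power sentence. In its place:
- State that the adjusted between-arm difference will be reported with its 95% CI.
- For the knowledge score only, state whether that interval, standardised by an SD named in advance (baseline, change or residual), excludes 0.334.
- If a power statement is still wanted, give it only at the pre-planned 0.334 with the achieved number per arm.

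This replaces one sentence. It costs nothing and changes neither recruitment, data collection nor the primary analysis.

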### Ethical Considerations

This study was approved by the NHG Domain Specific Review Board in Singapore (National Healthcare Group Domain Specific Review Board Ref: 2022/00479).

## Results

We plan to recruit 400 participants for the study by April 2023. Results are expected to be achieved by June 2023. The data analysis and manuscript are expected to be completed by September 2023.

## Discussion

### Overview

Our protocol describes an upcoming RCT to evaluate the effectiveness of an evidence-based serious game app in changing the KAP of antibiotic use and AMR among the public. There is currently a paucity of RCTs on the effect of serious game apps on health promotion and health behavior change due to the complexity of evaluating such studies in the population. Many clinical teams have developed stand-alone apps to solve clinical problems, but these apps are often not evidence-based or validated with population-based studies. The myriad of stand-alone apps causes app fatigue and is often unsustainable and limited in its outreach.

The few serious game app studies are targeted at improving physicians’ antibiotic prescribing habits [28]. These studies had limited success in changing physicians’ prescribing habits and antibiotic use in the community, as patients can influence physicians’ prescribing decisions. Since antibiotic prescribing is multifactorial [29,30], it is imperative to concurrently target public awareness of appropriate antibiotic use to slow the progression of AMR. To our knowledge, this is the first RCT that assesses the effect of a serious game app for public education on antibiotic use and AMR. We developed the app with a rigorous review of evidence from the literature and inputs from clinicians, game design specialists, allied health professionals, academics, computer engineers, and members of the public. Therefore, this study will provide us with a rare opportunity to assess the effectiveness of serious game apps in public education to address the threats of AMR.

